## Methods/design

### Aims and objectives

The main aim of the study is to evaluate the effect of IPS compared to high quality TAU offered to people with moderate to severe mental illness in six IPS centers located in different Norwegian counties. We aim to address the following questions:Is IPS more effective than high quality TAU in terms of increasing labor market participation?Is IPS more effective than TAU in terms of improving mental health status and quality of life?Are there specific Norwegian policy factors that will influence the effectiveness of IPS?What are the challenges of implementing and disseminating IPS in a Norwegian context?Is IPS cost-effective compared to TAU?

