The secondary outcomes, *mental health status, disability* and *quality of life*, will also be measured through survey questionnaires, in addition to questions on background and health-related variables:*Mental Health Status* will be measured using the 14-item Hospital Anxiety and Depression Scale (HADS), consisting of 2 subscales: anxiety (7 items) and depression (7 items) [36], and the 35-item Beliefs About Voices Questionnaire-Revised (BAVQ-R), consisting of 5 subscales: malevolence (6 items), benevolence (6 items), omnipotence (6 items), resistance (9 items), and engagement (8 items) [37].*Disability* will be measured using the 12-item version of the WHO Disability Assessment Schedule 2.0 (WHODAS 2.0), consisting of 6 different functioning domains: cognition (2 items), mobility (2 items), self-care (2 items), getting along (2 items), life activities (2 items), and participation (2 items) [38].*Health-related quality of life* will be measured using the health index from the EuroQol questionnaire (EQ-5D) [39].*Alcohol abuse* will be measured using the 3-item Alcohol Use Disorders Identification Test (AUDIT-C), screening test for heavy drinking and/or active alcohol abuse or dependence [40].*Drug abuse* will be measured using the Drug Use Disorders Identification Test (DUDIT), screening for drug use, drug-related problems, and/or drug dependence [41].*Subjective Health Complaints* will be measured by the 29-item Subjective Health Complaints Inventory (SHC), consisting of 5 subscales: musculoskeletal pain (8 items), pseudoneurology (7 items), gastrointestinal problems (7 items), allergy (5 items), and flu (2 items) [42].*Social support* will be measured using a revised 11-item version of the Social Support Inventory [43,44] using 2 subscales as suggested by Øyeflaten et al. [45]: directive social support (4 items) and nondirective social support (7 items).*Fatigue* will be measured by the 11-item Chalder Fatigue Questionnaire (CFQ) consisting of 2 subscales: physical fatigue (7 items) and mental fatigue (4 items) [46].

The questionnaire package was developed in collaboration with a client representative who provided input on the length, design and formulation of the information and questionnaires.

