**Sample size calculation with possible rates.**

There is, however, reason to believe that the target group in the current project is more heterogeneous than in the international studies, involving people with both moderate and severe mental illness. Furthermore, we anticipate that the high quality treatment as usual will result in higher competitive employment rates in the control group than in the international studies, particularly compared to US studies. We therefore aim to recruit between 400 and 500 participants.

Secondary outcomes are measured with questionnaire data, and we expect an approximate response rate of no more than 60%. This may have consequences for the conclusions drawn from secondary outcome data. However, compared to a previous IPS study [22] that found a significant effect on quality of life (mean 5.4, SD = 1.9 vs 4.8, SD = 1.7), the same difference could be detected with 142 participants in each group with a power of 80%, which in this project should be feasible even with a response rate of 60%. The analyses of the secondary outcomes will be performed with inverse probability weights to account for possible attrition bias [49].

Sufficient inclusion and response rates are crucial for enabling robust main analyses and for the possibilities to document effects of IPS with statistical certainty, as well as for allowing additional subgroup analyses. Rates lower than the estimated total sample size of 400–500 will reduce the chance of detecting smaller effects that may be important on a larger scale, and will limit the possibilities to further investigate which groups may benefit most from the intervention.

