#### Inclusion and exclusion

Inclusion criteria involved not working (unemployed, on sick leave, or on social benefits), undergoing treatment for moderate to severe mental illness, having an expressed desire to work, and sufficient Norwegian reading and writing skills to be able to fill out the questionnaires.

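### The BAVQ-R applies only to people who hear voices, yet it stands beside HADS as a measure of mental health status in a trial with no voices criterion

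*Protocol article*

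**What the plan says.** All references are to the protocol article.

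- **Aims and objectives.** The second question is posed for the whole trial population: "Is IPS more effective than TAU in terms of improving mental health status and quality of life".
- **Outcome measures.** Mental health status "will be measured using the 14-item Hospital Anxiety and Depression Scale (HADS), consisting of 2 subscales" (anxiety and depression), "and the 35-item Beliefs About Voices Questionnaire-Revised (BAVQ-R), consisting of 5 subscales: malevolence (6 items), benevolence (6 items), omnipotence (6 items", followed by resistance (9 items) and engagement (8 items). Quality of life "will be measured using the health index from the EuroQol questionnaire (EQ-5D"). Neither HADS nor EQ-5D is restricted to a subgroup.
- **Inclusion and exclusion.** Apart from not working, the criteria are "undergoing treatment for moderate to severe mental illness, having an expressed desire to work, and sufficient Norwegian reading and writing skills". There is no criterion on diagnosis, psychosis or voices.
- **Sample size calculation (text after Figure 1).** The authors expect that "the target group in the current project is more heterogeneous than in the international studies, involving people with both moderate and severe mental illness". The questionnaire response rate is put at no more than 60%. On missing questionnaires: "The analyses of the secondary outcomes will be performed with inverse probability weights to account for possible attrition bias".
- **Statistical analyses.** Analyses follow intention to treat, and the groups are compared on the survey outcomes at baseline, 6 and 12 months.
- **Randomization.** The baseline questionnaires are completed before the participant is allocated.

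**The concern.** By its name and its subscales, the BAVQ-R asks what a person believes about the voices he or she hears and how the person responds to them. It has no content for someone who hears none. Because the trial admits any moderate to severe mental illness, one of the two measures of mental health status does not apply to every randomized participant.

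Two consequences follow if the plan is applied as written.

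- If participants without voices are given a score anyway, it will presumably sit at the floor at every wave. They have no room to improve, and any effect on the scale is diluted.
- If only participants with a score at 6 or 12 months are compared, the set is defined by hearing voices after randomization. The article's Background argues that work improves psychiatric symptoms. Someone whose voices stopped under the better intervention would then leave the comparison because of that improvement. This is no longer an intention-to-treat comparison. Weights for attrition do not repair it, because the questionnaire was returned and the scale simply did not apply.

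At stake is how one secondary instrument is interpreted: a null or adverse BAVQ-R result could be read as a statement about mental health in the trial.

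**Working it through.** **1. Instrument against population.** The item counts under Outcome measures are consistent: 6 + 6 + 6 + 9 + 8 = 35. All five subscales belong to a questionnaire about voices. The inclusion criteria contain no voices criterion, and the target group is widened to moderate illness. The mismatch therefore stands in the text and does not depend on any figure.

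**2. The plan's own figure for a survey outcome.** The only sample size given for a secondary outcome is for quality of life: means 5.4 and 4.8, SDs 1.9 and 1.7, 142 per group, 80% power.

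- Common SD = √[(1.9² + 1.7²)/2] = √[(3.61 + 2.89)/2] = √3.25 = 1.803.
- Standardized difference d = 0.6/1.803 = 0.333.
- n per group = 2(1.960 + 0.842)²/d² = 2 × 7.849/0.1108 = 141.7, rounded up to 142.

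The stated 142 reproduces with a two-sided 5% level. That level is given for the primary outcome; two-sidedness and its use here are assumed.

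**3. Respondents per arm.** 200 × 0.60 = 120 and 250 × 0.60 = 150. The 60% is the article's upper expectation.

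**4. Respondents to whom the BAVQ-R applies.** The share hearing voices is not given. Shares from 10% to 50% are an assumption, with response taken as unrelated to hearing voices. Usable n per arm = 120 or 150 × share. The smallest difference detectable with 80% power and the power for d = 0.33 come from a two-sample t-test with equal arms, two-sided 5%.

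| Assumed share | n per arm | Smallest detectable difference (SD) | Power for d = 0.33 |
|---|---|---|---|
| 10% | 12–15 | 1.20–1.06 | 12–14% |
| 20% | 24–30 | 0.83–0.74 | 20–25% |
| 30% | 36–45 | 0.67–0.60 | 29–35% |
| 50% | 60–75 | 0.52–0.46 | 44–53% |
| Scale answered by all respondents | 120–150 | 0.36–0.32 | 73–82% |

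The value d = 0.33 is only a yardstick taken from the quality-of-life calculation. The article claims no power for the BAVQ-R.

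**5. What the table shows.** It shows imprecision in a subset. It does not measure the bias from voices stopping, which would need the rate at which they stop in each arm. The article gives no such rate.

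**The case against.** The strongest reply has four parts.

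- **The second question does not depend on the BAVQ-R.** HADS measures mental health status and EQ-5D measures quality of life, both without restriction to a subgroup. The article describes no composite of HADS and BAVQ-R, so an uninformative BAVQ-R score does not weaken HADS. This stands. A reader might infer that the second question cannot be answered; the document does not support that.
- **Who answers the scale, how it is scored and in which set it is analysed are details that an article leaves to the full protocol or analysis plan.** A filter item may already exist in the electronic questionnaire. This also stands, so the absence of such a rule is not the point made here. A rule could settle who answers, but it would not make the scale a measure for the whole population of the second question, and that is the role Outcome measures gives it.
- **Selection after randomization is conditional.** The article does not say that the comparison is confined to those with voices at follow-up. A reader might infer that the set shrinks as patients improve, or that most participants hear no voices. Both are plausible, but the document gives neither figure.
- **The direction of benevolence and engagement is not stated.** The article gives no scoring direction for any scale and cites the instrument's source, so this is not a separate fault. It does argue against ranking a person whose voices have stopped as the best value on those subscales.

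**Conclusion.** The concern holds in a limited form. Outcome measures fixes this outcome badly: a scale that presupposes hearing voices is one of two measures of mental health status in a trial that does not require voices. On its own it cannot show an effect on mental health across the randomized population. If it is compared among those with a score at 6 and 12 months, the set depends on a state that arises after randomization, which the stated weights do not cover.

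Under the assumed 10% to 50% share of voice hearers and 60% response, the comparison rests on about 12 to 75 per arm and could detect only differences of roughly 1.2 to 0.5 SD. These figures describe imprecision, and the size of any bias is unknown.

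Severity is minor to moderate. One secondary instrument is affected. HADS and EQ-5D still serve the second question, and the register-based primary outcome is untouched.

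**What to change.** - Name HADS as the measure of mental health status for the second study question, in all participants.
- Make the BAVQ-R exploratory. Analyse it by randomized group only among participants who report voices in the baseline questionnaire. That set is fixed before allocation.
- Keep in the set those whose voices have stopped. Report voices present or absent at follow-up as a separate explicit category, not as a missing value or a floor score. Do not rank it on the subscales. Present subscale scores among those who still hear voices as descriptive.
- Keep the inverse probability weights for unreturned questionnaires, and state that they do not cover returned questionnaires to which the scale does not apply.

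The cost is a change of wording and, if the questionnaire has none, one item asking whether the participant hears voices. If that item is used as a filter, participants without voices are spared 35 items. The downside is that the BAVQ-R loses its standing as a secondary outcome measure.

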### Data collection

Survey data will be collected from both groups at baseline, 6 and 12 month follow-up. Baseline questionnaires will be administered and collected at the IPS centers by the person conducting the recruitment interviews. Data will be collected using iPads with secure survey software (Qualtrics®), but paper questionnaires will also be available. Electronic data will be collected in offline mode, before being connected to the Internet at the IPS center and sent to a secure online database. Paper questionnaires will be temporarily stored at the IPS center and forwarded to Uni Research Health every three months. Follow-up questionnaires will be administered electronically to participants who provide their e-mail address at baseline, or on paper via regular mail if this is preferred.

Using data from the national social insurance register and the national employee-register in Norway allows for complete and objective data to be collected every month for every participant, with no loss to follow-up. Data will be collected retrospectively 3 years before baseline, and prospectively 4 years after baseline [47]. This information will be collected for each month of follow-up, to examine sensitivity of the primary 12-months results. Additionally, the long follow-up ensures comparison with a recent Swedish IPS study, where effectiveness was first seen at 18 months [32].

### Study design

The project is designed as a randomized controlled trial (RCT) using mixed methods, and includes: 1) an effect evaluation, 2) a process evaluation, and 3) a cost/benefit-analysis.

The effect evaluation is the main focus of the project, accompanied by a cost/benefit analysis to provide an economic assessment of the effect. However, in order to explore different stakeholders’ experiences and various facilitating factors and barriers in the implementation of the project, there is also a need for a process evaluation involving both qualitative and quantitative data.

### Effect evaluation

The effect evaluation is conducted as a RCT, which is the gold standard for clinical trials and ideal for achieving our aim of *comparing the effect* of different interventions to increase labor market participation.

#### Interventions

Participants will be randomly allocated to one of two groups, receiving different active interventions that aim to increase labor market participation and prevent withdrawal from the labor market. One group will receive *Individual Placement and support (IPS)* at their local IPS center, focusing on employment in the competitive labor market. IPS is a structured approach based on eight principles; competitive employment, eligibility based on client choice, integration of rehabilitation and mental health services, attention to client preferences, personalized benefits counseling, rapid job search (starting within one month), systematic job development, and time-unlimited and individualized support [19]. A pure control group with no intervention was considered to be neither feasible nor legally or ethically acceptable in this study. The other group will therefore be referred from the IPS center to NAV to receive a high quality version of *treatment as usual (TAU)*. This involves being offered a prioritized spot in a vocational rehabilitation scheme, primarily Work with assistance (AB) and/or Traineeship in a sheltered business (APS). AB involves assistance by a personal facilitator, and includes finding suitable work, negotiating wage and employment conditions, modified duties, and follow-up at the work place. APS involves testing of work capability within a sheltered environment doing tasks that are modified to individual skills and challenges, with follow-up as necessary by an advisor. Participants in this group may also be offered additional interventions based on the individual needs, as they normally would in TAU.

#### Participants and recruitment

Eligible participants are patients currently undergoing treatment for moderate to severe mental illness, who are currently out of the labor market but have an expressed desire to work. They could be either unemployed, on sick leave benefits, or on other social benefits at the time of inclusion. Participants will primarily be recruited from the various District Psychiatric Centers (DPS), which are placed in secondary care, but could also be recruited from stepped-care initiatives located in primary care. All participants are or will be connected to a treatment-team linked to a job specialist (caseworker trained in IPS). We aim to recruit 200–250 participants in each group, with a total sample size of 400–500.

#### Sample size calculation

Our estimates of sample size are based on international input-data from previous IPS-studies. As a general comparison, the typical sample size in the previous IPS studies range from 41 to 312 participants [33]. The studies from countries most similar to the Norwegian context include Australia (n = 41), England (n = 188), the Netherlands (n = 151), and Sweden (n = 120) [32,33]. For the non-US studies, the mean competitive employment rate was 50% for IPS and 20% for controls [33]. The study showing the lowest effect of IPS to this date came from England, with competitive employment rates of 22% for IPS and 11% for controls [48].

If we use 50% and 20% as possible rates, we will need 39 participants in each group in order to demonstrate a statistically significant difference (with a 5% significance level and power of 80%), and in a potential scenario with rates of 22% and 11%, we will need 178 participants in each group (Figure 1).

**Figure 1 Fig1:**
[figure not shown]
**Sample size calculation with possible rates.**

There is, however, reason to believe that the target group in the current project is more heterogeneous than in the international studies, involving people with both moderate and severe mental illness. Furthermore, we anticipate that the high quality treatment as usual will result in higher competitive employment rates in the control group than in the international studies, particularly compared to US studies. We therefore aim to recruit between 400 and 500 participants.

Secondary outcomes are measured with questionnaire data, and we expect an approximate response rate of no more than 60%. This may have consequences for the conclusions drawn from secondary outcome data. However, compared to a previous IPS study [22] that found a significant effect on quality of life (mean 5.4, SD = 1.9 vs 4.8, SD = 1.7), the same difference could be detected with 142 participants in each group with a power of 80%, which in this project should be feasible even with a response rate of 60%. The analyses of the secondary outcomes will be performed with inverse probability weights to account for possible attrition bias [49].

Sufficient inclusion and response rates are crucial for enabling robust main analyses and for the possibilities to document effects of IPS with statistical certainty, as well as for allowing additional subgroup analyses. Rates lower than the estimated total sample size of 400–500 will reduce the chance of detecting smaller effects that may be important on a larger scale, and will limit the possibilities to further investigate which groups may benefit most from the intervention.

#### Subgroups

Any significant main effects between the IPS intervention and control intervention group may allow for subgroup analyses. Regression analyses stratified on intervention group will additionally be conducted in order to study variables or sub-groups showing a stronger or weaker effect. The following a priori defined subgroups will be investigated: diagnostic groups (moderate vs. severe mental illness), work status at baseline (unemployed vs. disability benefits), and previous work history (previously employed vs. never been employed).

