#### Statistical analyses

The analyses will follow the “intention to treat” principle. We will apply administrative register data from NAV and SSB in order to evaluate the primary outcome of the project; labor market participation in ordinary paid employment and educational activity. Beyond giving consent at inclusion, this part of the effect evaluation is not dependent upon participants’ willingness to respond to surveys, as register data on employment, education and use of social security benefits will be complete for all participants. Consequently, common problems related to self-report such as recall bias, justification bias, and attrition will be avoided for our primary outcomes. Randomization helps to assure that there are no systematic differences between the IPS intervention and control intervention groups at baseline, in terms of both observable and unobservable characteristics. The design allows for a comparison of proportions employed in each group over time before and after inclusion, including a test of whether differences are statistically significant. Additionally, we will perform regression analysis using logistic regression models in order to a) control for any remaining variation in observable characteristics between groups, b) investigate which factors, other than IPS intervention, have an impact on labor market participation, and c) analyze heterogeneity in the response to IPS. Groups will be compared on secondary outcome measures using survey data at baseline, and after 6 and 12 months.

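### The Subgroups section looks for stronger or weaker IPS effects with regressions fitted within each arm, and states no between-arm comparison or treatment-by-subgroup interaction

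*Protocol article*

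**What the plan says.** Two sections of the protocol article bear on this.

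- **Subgroups.** It opens with a conditional statement: "Any significant main effects between the IPS intervention and control intervention group may allow for subgroup analyses". It then commits to a method: "Regression analyses stratified on intervention group will additionally be conducted in order to study variables or sub-groups showing a stronger or weaker effect". Three binary factors are listed, beginning "The following a priori defined subgroups will be investigated: diagnostic groups (moderate vs. severe mental illness". The other two are work status at baseline and previous work history.
- **Statistical analyses.** Logistic regression has three purposes: (a) adjustment for remaining differences between groups, (b) to "investigate which factors, other than IPS intervention, have an impact on labor market participation", and (c) to "analyze heterogeneity in the response to IPS". No model form is given for (c).

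Neither section mentions an arm-by-subgroup interaction or a formal comparison of coefficients between arms. The Sample size calculation section gives figures for main effects only. It does, however, name the wish to learn which groups benefit most as a reason for reaching 400–500 participants.

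**The concern.** Stratifying a regression on intervention group means fitting it separately in the IPS arm and in the TAU arm. Treatment is constant within each fit, so no coefficient can be an effect of IPS. A coefficient for severity in the IPS arm compares severe with moderate patients who all received IPS, which is a prognostic association. The sentence gives this method the task of finding where the effect of IPS is stronger or weaker, and the method does not estimate that unless the two fits are then contrasted.

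Without a stated contrast, the natural way to read two separate tables is to note which factors matter in one arm and not in the other. That reading confuses prognosis with effect modification. It is also sensitive to the arms having different event rates, and therefore different power. Severity and work history are both plausible predictors of employment whatever the intervention. Moderate against severe illness is a comparison of particular interest here, because the Background presents the inclusion of moderate illness as new. Advice on whom to offer IPS could come to rest on prognostic differences.

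**Working it through.** **1. The plan's own figures.** The sample size is set "with a 5% significance level and power of 80" per cent. With n per group = [1.96·√(2p̄(1−p̄)) + 0.8416·√(p₁(1−p₁)+p₂(1−p₂))]² / (p₁−p₂)²:

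- 50% vs 20%: (1.3221 + 0.5389)² / 0.09 = 3.4632 / 0.09 = 38.5, so 39.
- 22% vs 11%: (1.0288 + 0.4369)² / 0.0121 = 2.1484 / 0.0121 = 177.6, so 178.

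Both match the protocol. They concern main effects and say nothing about subgroup analyses. The rates are used below.

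**2. What within-arm fits estimate.** Write logit P(employed) = α + β·T + γ·X + δ·T·X, with T = 1 for IPS and X the subgroup.

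- The fit in TAU estimates γ.
- The fit in IPS estimates γ + δ.
- The question in the Subgroups section is about δ.

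Neither fit alone gives δ, but their difference does: (γ + δ) − γ = δ. On one simulated data set of 450 participants, the difference between arm-specific coefficients and the interaction coefficient from a joint model were both −0.1045, and both standard errors were 0.5158. The information is therefore in the two fits. What is missing is the step that extracts it.

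**3. Illustration: reading the fits arm by arm.** Assumptions that are not in the documents: a factor split 50/50 and an odds ratio of 2 in both arms (δ = 0). Arm sizes (200 and 250) and rates are the protocol's. There were 200,000 simulated trials per setting, with Wald tests at 5%.

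| Per arm | Rates IPS/TAU | Significant in IPS | Significant in TAU | In exactly one arm | Interaction test |
|---|---|---|---|---|---|
| 200 | 22%/11% | 50.6% | 30.2% | 50.0% | 4.4% |
| 250 | 22%/11% | 60.5% | 36.7% | 53.0% | 4.5% |
| 200 | 50%/20% | 70.2% | 47.7% | 51.1% | 4.7% |
| 250 | 50%/20% | 77.8% | 57.3% | 45.9% | 4.8% |

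The first row can be checked by hand. The arms are independent, so P(exactly one) = 0.506·(1 − 0.302) + 0.302·(1 − 0.506) = 0.353 + 0.149 = 0.502.

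**4. Power of the interaction test.** Now assume a true ratio of odds ratios of 2, with the factor not prognostic under TAU. For 22%/11% and 200 per arm (100 per cell), the subgroup rates are 28.5% and 16.6% under IPS and 11% twice under TAU.

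- Variance = Σ 1/(100·p·(1−p)) = 0.0491 + 0.0721 + 0.1021 + 0.1021 = 0.3255, so SE = 0.5705.
- ln 2 / 0.5705 = 1.215, and power ≈ Φ(1.215 − 1.96) ≈ 23%.

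Simulation gives 22% at 200 per arm and 27% at 250. At 50%/20% it gives 33–40%. For a ratio of 3 it gives 48–57% and 67–77% respectively.

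**5. Scale.** Under the assumptions of step 3 at 22%/11%, the subgroup rates are 27.8% and 16.2% under IPS, and 14.3% and 7.7% under TAU. The risk differences are 27.8 − 14.3 = 13.5 and 16.2 − 7.7 = 8.5 percentage points. There is no heterogeneity on the odds-ratio scale, yet there is on the risk-difference scale. Effects and test must therefore be reported on the same scale.

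**The case against.** **The method is not invalid in itself.** A reader might infer that arm-stratified regressions can never show for whom IPS works better. Step 2 shows otherwise: fitting the same model in each arm is equivalent to a fully interacted joint model. This objection stands, and the point is limited to the absence of any stated comparison.

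**The protocol sets no rule for comparing significance between arms.** A reader might infer from step 3 that the plan will mislabel prognostic factors in half of trials. The documents do not support that, because they never say effect modification will be declared from significance in one arm only. The figure is the cost of one reading that the wording leaves open.

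**Other routes exist.** The within-arm regressions are described as additional to subgroup analyses, and item (c) of Statistical analyses, listed apart from prognosis in (b), could hold an interaction term. This stands in part. Item (c) leaves room for a proper analysis, but the Subgroups section is the only place where a method for effect differences is named, and that method is the within-arm one.

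**Detail of this kind belongs in an analysis plan that is not shown.** That would answer a plain omission. Here the article does name a method, and the method does not by itself fit the purpose given for it.

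**Work history.** The third subgroup is "previous work history (previously employed vs. never been employed", while for register data "Data will be collected retrospectively 3 years before baseline". A reader might infer that people who never worked cannot be identified. The documents do not support this: they do not say that the subgroup comes from the register, and the questionnaires include background questions. It forms no part of the point.

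**Conclusion.** The point holds in a limited form. The Subgroups section plans within-arm regressions to find stronger or weaker effects of IPS and states no between-arm comparison or interaction. Taken by themselves, those regressions describe predictors of employment under each intervention.

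The gap between reading the fits arm by arm and testing the interaction is large: about half of trials against about 5%. That contrast rests on an assumed odds ratio of 2, a 50/50 split and a reading that the protocol does not prescribe. The algebra in step 2 needs none of these assumptions.

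The matter concerns secondary subgroup analyses. The intention-to-treat comparison of proportions and the sample size figures are untouched. It is worth correcting because learning which groups benefit is a stated purpose and the correction is nearly free.

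**What to change.** Replace the sentence on stratified regressions with wording to this effect:

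*For each of the three a priori subgroups, heterogeneity of the IPS effect will be assessed in one model of all randomized participants with terms for arm, subgroup and arm-by-subgroup. The IPS–TAU effect with 95% CI in each subgroup, and the interaction estimate with CI and test, will be reported on the same stated scale. These analyses are exploratory. Regressions within each arm describe prognosis only.*

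The scale should be named in advance. Either use odds ratios throughout, with the ratio of odds ratios as the interaction, or risk differences throughout, with their difference as the interaction. An odds-ratio test should not be paired with risk differences, for the reason in step 5. Item (c) of Statistical analyses should refer to this model, and the within-arm regressions should move under item (b).

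The cost is a change of wording and three models, with no new data. The drawback is low power: about 22–27% for a ratio of odds ratios of 2 at 22% vs 11%. Intervals will be wide, and a non-significant interaction must not be read as evidence of a uniform effect.
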